## Abstract

**Background:**

Although the mental and physical benefits of physical activity are well-established, there is a racial/ethnic disparity in activity such that minorities are much less likely to engage in physical activity than are White individuals. Research suggests that a lack of motivation may be an important barrier to physical activity for racial/ethnic minorities. Therefore, interventions that increase participants’ motivation may be especially useful in promoting physical activity within these groups. Physical activity interventions that utilized the clinical technique of motivational interviewing (MI) in conjunction with the theoretical background of self-determination theory (SDT) have been effective in increasing White individuals’ physical activity. Nevertheless, it remains unclear the extent to which these results apply to minority populations.

**Methods/Design:**

The current study involves conducting a 12-week physical activity intervention based on SDT and MI to promote physical activity in a racially/ethnically-diverse sample. It is hypothesized that this intervention will successfully increase physical activity in participants. Specifically, it is expected that minorities will experience a greater relative increase in physical activity than Whites within the intervention group because minorities are expected to have lower baseline levels of activity.

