### Hypotheses for the primary outcome: physical activity

*Hypothesis 1A*: White participants will report engaging in more physical activity than participants from minority groups at baseline (i.e., a significant main effect of race/ethnicity).
*Hypothesis 1B*: There will be a greater increase in physical activity from baseline among the intervention groups than among the control groups (i.e., a significant main effect of condition).
*Hypothesis 1C*: There will be a greater increase in physical activity from baseline for minority participants in the intervention groups than White participants in the intervention groups (i.e., a significant race/ethnicity by condition interaction).
*Hypothesis 1D*: Participants in the intervention groups will experience a greater increase in need fulfillment during exercise (i.e., autonomy, competence, relatedness and intrinsic motivation) which will mediate the effect on physical activity.$$ Condition\to Need\  Fulfillment\to Physical\  Activity $$

*Hypothesis 1E*: Participants in the intervention condition will report that their instructor utilizes MI skills more frequently which will mediate the effect on physical activity.$$ Condition\to Instructor\hbox{'}s\  Perceived\  use\  of\ MI\  Skills\to Physical\  Activity $$

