### Participants

An a priori ANOVA power analysis was conducted to determine how large a sample would be needed to detect significant main effects and interactions (G*Power version 3.1.3., 2010). This was estimated using a large effect size (f = 0.50), an alpha level of 0.05, and the power was estimated at 0.80. This power analysis determined that 48 participants are needed in the sample in order to detect a statistically significant change in an effect of this size.

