#### Participants recruited

Participants were recruited using online advertisements (YMCA Facebook website) and hard-copy advertisements that were displayed at the YMCA and throughout the city of Syracuse at public libraries, community centers, churches, etc. If the YMCA members were interested in participating, they completed a survey online through Qualtrics or a hard copy version of the survey in order to determine whether they were eligible to participate in the study. The inclusion criteria mandated that participants were currently healthy enough to exercise once a week, not be pregnant or planning to get pregnant within the next 3 months, were willing to attend an exercise class once a week for 12 weeks, were willing to complete questionnaires at baseline and 12 weeks, allowed the intervention staff to monitor their attendance at the YMCA for 6 months post intervention, and allowed the exercise instructor to create an audio recording of all of the intervention sessions.

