#### Intrinsic motivation for exercise

Individuals’ motivation for exercise will be assessed using the 15-item Behavioural Regulation in Exercise Questionnaire (BREQ) by Mullan, Markland & Ingledew [66]. This measure includes four subscales, which are external regulation (e.g., “I feel under pressure from my friends/family to exercise”), introjected regulation (e.g., “I feel guilty when I don’t exercise”), identified regulation (It’s important to me to exercise regularly”) and intrinsic regulation (e.g., “I exercise because it’s fun”) in regards to engage in physical activity behavior. The BREQ was selected over the BREQ-2 (a measure which includes four items assessing amotivation) due the fact that the experimenter expected participants to have some motivation to exercise due to the fact that they volunteered to attend a weekly exercise class; hence, it is expected that adding the amotivation subscale would be of little benefit. Although integrated regulation is not included in the BREQ, Wilson, Rodgers, Loitz, and Scime [67] created a 4-item subscale to assess integrated regulation (e.g., “I consider physical activity consistent with my values”) which is meant to be used in conjunction with the BREQ and will be utilized in the current study.

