## Discussion

Despite the evidence that interventions based on SDT and MI are effective in increasing White individuals’ physical activity, the combined efficacy of SDT and MI interventions on physical activity within minority groups has yet to be examined. The current study will determine whether SDT and MI-based interventions can be used to decrease the racial/ethnic disparity in physical activity.

This study has a number of strengths. A carefully designed, clinically- and theory-driven intervention will be used. Additionally, a rigorous treatment fidelity assessment will be conducted to determine the extent to which the exercise instructors followed the research protocol and utilized MI and SDT techniques during the intervention, the effect of the intervention exercise, and ways to improve the quality of future studies.

The current study also has limitations. The primary outcome in this study is level of physical activity, which will be assessed using a self-report measure (i.e., the IPAQ) rather than an objective measure of activity. This method was chosen because the IPAQ is a valid measure to assess individuals’ overall level of physical activity [63]. Future studies should utilize self-report measures, as well as objective measures of activity. Another study limitation stems from the fact that the racial/ethnic composition of the exercise instructors in this study does not match the racial/ethnic composition of the sample. Research suggests that, “A culturally centered intervention must consider the role of ethnic and racial similarities and differences in the client–therapist dyad. This dimension brings into focus the consideration of ethnic and race matching in the client–therapist dyad, as it may be important to acknowledge ethnic, racial, or cultural similarities and differences.” [70, 71]. Unfortunately, only White instructors are available to teach at the Southwest Syracuse YMCA and the Downtown Syracuse YMCA during the course of the intervention, and certain classes that are predominantly composed of minorities will not be taught by an instructor who is a racial/ethnic minority.

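### The Discussion promises an answer on decreased racial/ethnic disparity, but no planned analysis estimates that disparity

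*Protocol article*

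**What the plan says.** The Discussion of the protocol article sets the aim: "The current study will determine whether SDT and MI-based interventions can be used to decrease the racial/ethnic disparity in physical activity". It names no test or estimate for that conclusion.

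Two hypotheses for the primary outcome involve race/ethnicity. 1A expects White participants to be more active than minority participants at baseline. 1C expects a larger increase in minority than in White participants of the intervention groups, shown by "a significant race/ethnicity by condition interaction". The abstract (Methods/Design) words 1C as a greater relative increase and gives the reason: "because minorities are expected to have lower baseline levels of activity".

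The section on planned statistical analyses assigns 1A, 1B and 1C to one 2 x 2 factorial ANCOVA of the IPAQ, with pretest scores as covariates. Neither 1C nor the Discussion's conclusion is made to depend on 1A.

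On the sample, the recruitment section requires that participants "were willing to attend an exercise class once a week for 12 weeks". The section on intrinsic motivation explains the choice of questionnaire by saying that "the experimenter expected participants to have some motivation to exercise due to the fact that they volunteered to attend a weekly exercise class".

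**The concern.** A disparity has decreased only if there was a gap and it ended nearer zero. An interaction shows neither. It says that the intervention effect differs by race/ethnicity and is silent on where the White-minority gap starts or finishes.

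The hypothesis that could supply the starting point, 1A, is given a model that cannot test it. The background expects a gap from a study of more than 11,000 people, whereas this sample consists of volunteers for a weekly class, and the size of the gap among them is unknown. If it is small, a significant 1C means that minority participants overtook White participants. Reporting that as a reduced disparity would misstate the article's main public-health conclusion.

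**Working it through.** **1. The plan's own figure.** Inputs from the Participants section: f = 0.50, alpha 0.05, power 0.80. The noncentrality is N x f^2 = 48 x 0.25 = 12. With four cells (3 and 44 degrees of freedom) power is 0.803, so the stated 48 reproduces and is not in question. For a one-degree-of-freedom interaction in a balanced 2 x 2, f = 0.50 is a difference in differences of 4 x 0.50 = 2 SD.

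**2. What 1C estimates.** Let gC and gI be the White-minus-minority gaps at week 12 in the control and intervention arms. With randomisation within race/ethnicity strata, the interaction in favour of minorities estimates d = gC - gI. The same d = 1 SD arises from:
- gC = 1, gI = 0 (gap closed);
- gC = 0.5, gI = -0.5 (gap reversed, same size);
- gC = 0, gI = -1 (gap created);
- gC = -0.5, gI = -1.5 (reversed gap widened).

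Since gI = gC - d, the intervention-arm gap is the smaller in absolute size only if gC > d/2.

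**3. How large d must be to reach significance.** Table 1 gives 15 White and 12 minority participants in the intervention arm, 16 and 14 in control. SE = sqrt(1/15 + 1/12 + 1/16 + 1/14) = 0.533 residual SD. With t(52) = 2.007 the threshold is 2.007 x 0.533 = 1.07 residual SD. Multiplying by sqrt(1 - r^2) gives 0.93 raw SD at an assumed pre-post correlation r = 0.5 and 0.76 at r = 0.7. So, apart from chance baseline imbalance, any significant 1C implies a larger absolute gap in the intervention arm unless the control-arm gap exceeds about 0.38 to 0.47 SD (half of 0.76 and 0.93).

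**4. Simulation of the planned ANCOVA** (Table 1 cells; SD 1; correlations, gaps and effects assumed, because the article gives none).

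With r = 0.5 and an extra benefit of 1 SD in minorities, 1C is significant in 55-56% of trials at every gap tried, so the test does not respond to the gap:

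| True gap (SD) | 1C significant | Of these, intervention-arm gap wider in absolute size at week 12 than at baseline |
|---|---|---|
| -0.5 | 56% | 100% |
| 0 | 56% | 97% |
| 0.5 | 56% | 60% |
| 1.0 | 55% | 10% |

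With r = 0.6 and an extra benefit of 0.5 to 1.0 SD, comparing the arms at week 12 among trials with a significant 1C:

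| True gap (SD) | Absolute gap larger in intervention than control arm |
|---|---|
| 0-0.3 | 45-97% |
| 0.5 | about 20-50% |
| 0.8-1.0 | about 1-13% |

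**5. Why the ANCOVA cannot test 1A.** Suppose a stable true gap of 0.5 SD, r = 0.5 and an extra benefit of 1 SD in minorities. Adjusted for pretest, the White-minus-minority difference at week 12 is 0.5 x (1 - 0.5) = 0.25 in control and 0.25 - 1 = -0.75 with the intervention. The average race effect is (0.25 - 0.75)/2 = -0.25. The baseline gap is +0.5, yet the term assigned to 1A has the opposite sign. It is a baseline-adjusted week-12 difference that also absorbs half the interaction.

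**6. A relative increase is not a narrower gap.** If scores of 1000 and 1500 both rise by 500, the gains are +50% and +33%, and the gap stays at 500.

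**7. What an unadjusted baseline test could show.** With 31 White and 26 minority participants, SE = sqrt(1/31 + 1/26) = 0.266 SD. Power is 20%, 46% and 84% for gaps of 0.3, 0.5 and 0.8 SD.

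**The case against.** Four points against the concern have force.

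- **A stated reporting rule.** A reader might infer that the plan would declare a decreased disparity on a significant 1C. The article does not say so. The Discussion sentence is a general aim, and 1C is worded only as a greater increase in minorities. The link is an inference, drawn because 1C is the only hypothesis on a differential effect by race.
- **A gap merely assumed.** A reader might infer that the plan never looks for a gap in its own sample. It does: 1A prespecifies one. What fails is the model given to 1A and the lack of any link from 1A to the conclusion.
- **A gap known to be small.** A reader might infer that selecting willing exercisers has removed the gap. The documents do not show this. They speak of some motivation, list no activity criterion, and describe advertising at libraries, community centers and churches. Take a population gap of 0.5 SD, the most willing 20% volunteering, and a willingness-activity correlation of 0.5. The gap stays at 0.50 if willingness is equally distributed across groups and becomes 0.40 if willingness depends on activity alone. It falls to about 0.30 only on a further assumption, such as minorities being about 0.5 SD less willing. At gaps of 0.8-1.0 SD the problem is small.
- **The population reading.** The Discussion may mean the population disparity, for which larger benefit in minorities is relevant evidence whatever the gap here. That is fair, but it makes the conclusion an extrapolation from volunteers rather than something the trial will determine.

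Routine reporting of group means might also reveal the gap. That does not repair 1A, whose test the article itself fixes.

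**Conclusion.** The concern holds in a limited form. The article promises a conclusion about disparity that none of its planned analyses estimates: 1C does not depend on the size or sign of the gap, and 1A as assigned cannot detect a baseline gap. Both statements follow from the model and need no assumed figures.

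How far a significant 1C would mislead does depend on assumptions about the gap, the effect and the pre-post correlation. It is serious at true gaps of about 0 to 0.5 SD and minor at 0.8 to 1 SD, and the documents do not say where this sample lies. No stated figure is wrong. This should be corrected before analysis, with medium confidence in its practical size.

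**What to change.** - Test 1A on baseline IPAQ scores without pretest adjustment.
- Report the White-minus-minority IPAQ gap at baseline, and at week 12 in each arm, unadjusted for pretest, with 95% CIs.
- Base any statement on decreased disparity on those estimates and their CIs, not on a significant 1C alone or on the signs of point estimates. With a true gap of 0.3 SD, the observed baseline gap would be zero or reversed in 13% of trials by chance. Otherwise report 1C only as a difference in intervention effect by race/ethnicity.
- State that the disparity result applies to YMCA volunteers for a weekly class.

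The cost is one extra table from scores the ANCOVA already needs, some rewording, and possibly a narrower headline claim. The intervals will be wide. The SE of the week-12 gap is sqrt(1/15 + 1/12) = 0.39 SD in the intervention arm and sqrt(1/16 + 1/14) = 0.37 SD in control, so the trial may leave the question open. Reporting that openly is better than settling it with a test of something else.

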**Discussion:**

Results from this study will give us a greater understanding of the generalizability of SDT interventions designed to improve motivation for physical activity and level of physical activity.

**Trial registration:**

Clinical Trials Gov. Identifier NCT02250950 Registered 24 September 2014.

## Background

The mental and physical benefits of engaging in physical activity are well-documented. Research suggests that regular physical activity decreases individuals’ risk of depression and anxiety, cardiovascular disease, diabetes, multiple types of cancer, and reduces the likelihood that individuals will die prematurely [1–3]. Clearly, encouraging people to engage in physical activity is a major priority within the field of Public Health.

According to the Centers for Disease Control and Prevention (CDC), it is important to increase the proportion of adults who engage in moderate intensity aerobic activity for at least 150 min/week, vigorous intensity for 75 min/week, or an equivalent combination [4]. In addition to aerobic activity, the CDC recommends that adults engage in muscle-strengthening exercises on two or more days a week in order to work all major muscle groups, such as legs, hips, back, abdomen, chest, shoulders, and arms [4].

### Physical activity in minority groups

Racial/ethnic minorities are especially unlikely to engage in physical activity and tend to have poorer health outcomes. In a study with over 11,000 participants, researchers found that non-White participants were significantly less likely to engage in ideal levels of physical activity (i.e., at least 150 min of physical activity per week) than were White participants [5]. Minorities also are at an increased risk for developing obesity, heart disease, and stroke - diseases that are influenced by physical inactivity [6, 7].

There are many possible reasons why minorities engage in less physical activity. Specifically, environmental barriers to physical activity, such as not having access to gyms or parks and the belief that one’s neighborhood is not safe, have been widely reported [8–10]. Social and cultural factors, such as the lack of support from family and friends, and the perception that African Americans have more physically demanding work and less free time than other groups, also impact minorities’ likelihood of exercising [11]. Additionally, research suggests that psychological factors, such as lack of motivation, enjoyment, and self-efficacy, are especially important in understanding why minorities are less likely to engage in physical activity [12–14]. These environmental, social, and cultural barriers to physical activity contribute to minorities’ lack of motivation for physical activity [15]. However, rather than attempting to modify the social, cultural, and environmental factors that thwart participants’ motivation engage in physical activity, we seek to directly manipulate motivation. The exercise instructors in the current intervention will utilize motivational theories and clinical techniques in order to promote participants’ motivation to engage in physical activity.

### SDT & MI interventions

Because minority groups report less motivation to engage in physical activity, interventions that increase participants’ motivation may be essential in order to promote physical activity within these populations. Self-determination theory (SDT) is one theory that can be used to understand factors that drive motivation. According to SDT, humans are driven by three innate psychological needs: autonomy, competence, and relatedness [16]. Autonomy is defined as “experiencing a sense of choice, willingness, and volition as one behaves” [17]. Competence implies that one is able to affect the environment and to attain desired outcomes within it [18]. Lastly, relatedness refers to the desire to feel connected to others [19].

Self-determination theory states that the extent to which people are able to fulfill these three basic psychological needs has a profound impact on their mental and physical health outcomes. People who report greater autonomy, competency, and relatedness (i.e., who have high need fulfillment) tend to experience more positive mental health outcomes, as well as more positive physical health outcomes [20–23]. Given that individuals’ trait levels of self-determination can predict their mental and physical health, researchers have tried to enhance participants’ autonomous motivation within interventions to promote positive health behaviors or to prevent negative health behaviors.

Physical activity is one important health behavior that health researchers have tried to promote using interventions based on SDT. Although research shows that people acknowledge the many health benefits of physical activity, motivation to engage in physical activity may decline if individuals’ physical activity environment does not support their autonomy, competence, and relatedness [24–26]. Research suggests, however, that interventions derived from SDT can be used to re-establish participants’ intrinsic motivation by providing a need-supportive environment. After SDT physical activity interventions participants report that physical activity is interesting, challenging and enjoyable and that physical activity produced an increase in participants’ self-reported happiness and vitality [27, 28]. Given that engaging in physical activity results in positive emotions and attitudes, physical activity interventions should produce greater intrinsic motivation than interventions that target less intrinsically-motivated health behaviors (e.g., medical testing, dietary control, dental hygiene, etc.).

Additionally, the therapeutic approach of motivational interviewing (MI) has been used in conjunction with SDT. Motivational interviewing is a client-centered counseling style for eliciting behavior change by encouraging clients to explore and resolve ambivalence [29]. The four general principles of MI involve expressing empathy, developing discrepancy, “rolling with resistance,” and supporting self-efficacy [30]. First, the MI-adherent counselor must express empathy towards the client because people are more engaged when they feel accepted and valued. Second, when individuals experience discrepancy between their current behavior (e.g., leading a sedentary life) and their personal core values or life goals (e.g., their desire to be physically healthy), this motivates individuals to align their behaviors with their values and goals. Third, MI states that the therapist should encourage participants to explore their ambivalence, rather than argue for change, which could actually make participants resistant to change. Fourth, supporting self-efficacy is important in MI because participants are more likely to try to change their behavior if they believe that they have the resources to overcome barriers and to achieve desired outcomes. These four principles of MI encourage people to engage in “change talk” – to verbalize their ability, desire, need, and reasons to change their current behavioral patterns. This change talk increases participants’ commitment to change, which predicts actual behavior change [29].

Many researchers have commented on the ways in which the combined effect of these two theories could be used to elicit greater behavior change [31–36]. Specifically, SDT may be used to explain how and why MI interventions work by providing psychological mediators that explain MI intervention efficacy [34]. SDT interventions can also be used to create need-supportive environments which bolster participants’ motivation to engage in desired behaviors [37]. Additionally, MI can provide SDT researchers with a concrete set of methods (e.g., reflective listening and open-ended questioning), which have been shown to increase participants’ motivation to change their behavior [36]. As argued by Vansteenkiste and Sheldon [36], combining the applied approach of MI and the theoretical approach of SDT should be beneficial to the progress of both motivational perspectives. Many research articles have discussed the theoretical importance of using SDT and MI within interventions [31–36]. Other research has demonstrated that SDT and MI interventions impact participants’ physical activity [38–41].

Although there is evidence that interventions based on both SDT and MI are effective in promoting greater physical activity, this has been studied among primarily White samples and there is a dearth of information on their effect on physical activity within minority groups [38, 40, 41]. There is, however, evidence for the efficacy of interventions based on SDT and MI, when used separately within minority populations. The previous research has found that MI produces greater behavioral change within domains such as alcohol use, smoking, drugs, HIV, treatment engagement, diet, physical activity, eating disorders, and gambling among minorities (e.g., African Americans) than Whites [42]. Due to the greater efficacy of MI within minority populations, it has been proposed that MI may be especially effective for individuals who are resistant or less ready for change [43]. There is also empirical and theoretical support for the efficacy of self-determination theory interventions on physical activity in minority populations. Previous intervention studies have shown that SDT interventions are effective in promoting physical activity among minorities [44–46]. In terms of theoretical support, the degree to which a culture is supportive can impact individuals’ need fulfillment [16]. Cultural norms in minority groups dictate that health promotion behaviors, such as engaging in physical activity, are viewed as White middle-class behaviors; whereas unhealthy behaviors, such as not engaging in physical activity, are viewed as in-group defining [47]. Therefore, there may be less support for physical activity within minority communities, causing minority individuals to experience less need fulfillment within this domain. Interventions based on SDT are designed to increase need fulfillment within the desired domain. Hence, it is reasonable to expect that a physical activity intervention based on SDT would facilitate greater need fulfillment for activity in minorities. Despite the evidence that separate interventions based on either MI or SDT are effective in helping participants to increase their physical activity, the combined efficacy of interventions based on both SDT and MI on physical activity within minority groups has yet to be examined.

Given that interventions based either on the theoretical perspective of SDT or the clinical perspective of MI have been shown separately to be effective in promoting health behaviors in minority populations, and that interventions combining techniques from these clinical and theoretical backgrounds have been shown to be especially effective in promoting physical activity (in largely White samples), it stands to reason that a physical activity intervention combining SDT and MI techniques would be the best option to motivate minority groups to engage in physical activity. The current study will utilize a physical activity intervention based on SDT and MI to examine the following hypotheses.

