#### Assignment to condition

The current study is a parallel group, two arm, superiority trial with 1:1 allocation ratio. First, participants were allowed to choose whether they wanted to attend the Downtown YMCA or Southwest YMCA. Next, stratified randomization was employed such that participants were separated by race/ethnicity (i.e., minority versus non-minority) and participants were randomly assigned to the control or intervention condition within each site. A computer-generated allocation sequence was used and assignment to condition was made using sequentially numbered, opaque, sealed envelopes. Throughout the study, participants and the research assistant (i.e., an outcome assessor) will remain blind to condition. Due to the nature of the study, the exercise instructors and the experimenter (i.e., an outcome assessor and data analyst) will not be blind to condition.

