### Planned statistical analyses

The analysis plan involves a 2 (race/ethnicity) × 2 (condition: intervention vs. control) factorial ANCOVA with pretest scores entered as covariates to test Hypotheses 1A-1C involving physical activity (assessed by the International Physical Activity Questionnaire [63]). Analysis of variance will be used to test Hypothesis 2A involving need fulfillment (assessed by the Basic Psychological Needs in Exercise Scale [65] and the Behavioural Regulation in Exercise Questionnaire [66]), physical activity adherence (assessed by how often participants attend the YMCA six months post-intervention), and psychological well-being (assessed by the Psychological General Well-being Index [64]). When examining whether mediators account for the relationship between intervention condition and physical activity, the Preacher and Hayes [69] nonparametric bootstrap approach will be used (i.e., Hypothesis 1D using the Basic Psychological Needs in Exercise Scale [65] and the Behavioural Regulation in Exercise Questionnaire [66] and Hypothesis 1E assessed by the Client Evaluation of Motivational Interviewing Scale [60]).

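### The stated 1D mediation model omits race/ethnicity, a randomisation stratum, and could declare mediation falsely if gains differ strongly by race; in 2A the omission costs only precision

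*Protocol article*

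**What the plan says.** Under Assignment to condition, randomisation was stratified within site: "participants were separated by race/ethnicity (i.e., minority versus non-minority").

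The protocol links this factor to both ends of the 1D path.

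- **Activity.** Physical activity in minority groups reports that non-White people are less active. Hypothesis 1A expects the same at baseline. Hypothesis 1C expects a larger gain for minority than for White participants in the intervention, which it describes as "a significant race/ethnicity by condition interaction".
- **Need fulfillment and motivation.** SDT & MI interventions says that minority groups report less motivation and may experience less need fulfillment for activity, and adds that "it is reasonable to expect that a physical activity intervention based on SDT would facilitate greater need fulfillment for activity in minorities". Hypothesis 1D counts intrinsic motivation as part of need fulfillment.

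Planned statistical analyses gives Hypotheses 1A to 1C a race/ethnicity by condition ANCOVA with pretest covariates. For the secondary outcomes it says "Analysis of variance will be used to test Hypothesis 2A", and the hypothesis itself concerns a main effect of condition. The bootstrap for 1D and 1E is introduced with "When examining whether mediators account for the relationship between intervention condition and physical activity". No race term and no pretest is named for 1D, 1E or 2A. None is expressly excluded either.

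**The concern.** Randomising condition protects the condition-to-mediator path and the total effect of condition. It does not protect the mediator-to-activity path. If minority participants in the intervention arm gain more on need fulfillment and, independently, more on activity, the two gains are correlated within that arm even when needs have no effect on activity. A model without race/ethnicity reads this correlation as mediation, in the direction that 1D predicts. A significant 1D result could then not be told apart from a true 1C.

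For 2A the question is a smaller one: whether a factor used in randomisation is left in the error term.

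**Working it through.** **Inputs from the documents.** Table 1: 27 intervention and 30 control participants. Minority participants number 9 + 3 + 0 = 12 of 27 (44.4%) and 11 + 1 + 2 = 14 of 30 (46.7%), so 26 of 57 overall. Participants section: f = 0.50, alpha 0.05, power 0.80, N = 48.

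**The plan's own figure.** With a noncentral F and lambda = f² × N, a 3-df test over four groups gives N = 48 (power 0.803). A 1-df main effect or interaction would need 34 (36 if balanced). The 48 therefore reproduces, as a 3-df test, and is not disputed here.

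**Assumed, not in the documents.** White gain in the intervention arm 0.5 SD on mediator and activity; extra minority gain d in that arm; true mediator-to-activity effect zero.

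**1D, large-sample bias without a race term.** The extra gain adds to the mediator's variance, and to its covariance with activity, within arms:

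v = (27/57) × (12/27) × (15/27) × d² = 0.117 d²

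The spurious slope is b = v/(1 + v), the condition effect on the mediator is a = 0.5 + (12/27)d, and the spurious indirect effect is ab. At d = 1: b = 0.117/1.117 = 0.105, a = 0.944, ab = 0.10 SD. At d = 0.5: b = 0.028, a = 0.722, ab = 0.02 SD.

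**1D, false mediation at n = 57** (share of 95% percentile-bootstrap intervals that exclude zero; 600 trials, 500 resamples; no baseline gap, d in residual SD):

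| d on both | No race | Race only | Race and race × condition |
|---|---|---|---|
| 0 | 1.5% | 1.7% | 2.2% |
| 0.5 | 4.7% | 4.5% | 4.8% |
| 1 | 14.0% | 10.3% | 6.3% |
| 1.5 | 43.5% | 20.5% | 7.0% |
| 2 | 71.2% | 34.7% | 5.7% |

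**With both pretests in the model**, repeated runs gave without race:

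- about 6% at 0.5 SD on both;
- 14.5-18% at 1 SD on both;
- 31-33% at 1 SD on needs and 2 SD on activity.

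With race and race × condition the rates were 5-8%. A race main effect alone left 13.5% and 20% in the last two scenarios. With 400 trials, the simulation standard error near 15% is √(0.15 × 0.85/400) = 1.8 points.

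**Where 2 SD comes from.** In a balanced 2 × 2 layout, f = 0.50 placed wholly on the interaction means a difference of differences of 4 × 0.50 = 2 SD. Because N = 48 matches the 3-df test, that reading needs both main effects to be zero, so 2 SD is an upper end and not an expectation.

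**2A, bias.** With White gain 0.5 and extra minority gain 1, the average effect is 0.5 + 26/57 = 0.956. The condition-only ANOVA gave 0.942 and the race-adjusted models 0.953-0.954, so there is no material bias.

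**2A, precision.** Interval widening is √(1 + p(1 − p)g²) with p = 26/57 and race gap g. At g = 0.5 it is √(1 + 0.248 × 0.25) = 1.03, and at g = 1.0 it is √1.248 = 1.12. Type I error without race was 4.4% and 2.9% at these gaps, against 5.0% adjusted. Power at a 1 SD gap and a condition effect of 0.5 SD was 39.5% against 45.6%.

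**The case against.** **Silence is not exclusion.** This is a condensed article, and covariates for mediation and secondary models are often left to the analysis plan. That stands as a limit: one cannot say that the investigators have ruled race/ethnicity out. The point keeps its force because the same paragraph does name race/ethnicity and pretests for 1A to 1C.

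**The need-fulfillment premise is thin.** A reader might infer that the protocol predicts larger need gains in minorities than in Whites. It does not say so. The Background sentence names no comparator, follows a remark about lower need fulfillment, and can mean more than before. No numbered hypothesis states race by condition for needs. The Abstract's version of 1C speaks of a relative increase attributed to lower baseline activity, which is compatible with little difference in absolute gain. This stands, so the link to needs is plausible and not predicted.

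**The large rates need large gaps.** This also stands. At 0.5 SD, leaving race out does no harm. If race modifies need gains only (1 SD) and not activity independently, the rates are 7.0% without race and 6.7% with it. Rates of up to 36% arise from baseline gaps of 0.5-1.0 SD when pretests are also left out, but 1D concerns an increase, so those are not a fair headline.

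**2A.** A reader might infer that racial differences could also pass as an effect there. They cannot: 2A compares randomised arms balanced on race by stratification. Its wording about a main effect could even be read as the same factorial layout used for 1B. Nor do the documents state race gaps in well-being or attendance.

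**The remedy can do harm if coded carelessly.** With 0/1 coding and White as reference, the condition coefficient belongs to White participants alone. In simulations with a true path, power fell from 45-88% to 14-29% under one set of assumptions and from 82-94% to 32-36% under another. Averaging over race or mean-centring restored it to 42-89% and 73-82% respectively. The fix must therefore state the coding.

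**Conclusion.** The concern holds for 1D, conditionally. Race/ethnicity is a randomisation stratum, an expected modifier of activity gain and a plausible modifier of need fulfillment, and the stated mediation model does not include it. False mediation is negligible if minority and White gains differ by about 0.5 SD (5-6%). It is material at about 1 SD on both (14-18%) and about 30% at 1 SD on needs with 2 SD on activity. With race and race-by-condition it is 5-8%. The documents do not give these differences, so the size is a range over assumptions and not an estimate.

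For 2A the loss is precision only, with a slightly conservative test. For 1E the case is precautionary: all instructors are White and the Discussion raises racial matching, but nothing states that perceived MI use differs by race. Severity is minor to moderate.

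**What to change.** In Planned statistical analyses:

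- **2A:** include race/ethnicity, as randomised (minority versus non-minority), as a factor, stated to be for precision.
- **1D:** include baseline mediator, baseline activity, race/ethnicity and race/ethnicity-by-condition in both the mediator and the activity equations. Mean-centre race/ethnicity, or average the indirect effect over the sample's race distribution, and say so, so that one overall indirect effect is tested and not that of the White reference group.
- **1E:** include race/ethnicity as a covariate, as a low-cost precaution.

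The cost is one or two degrees of freedom. An activity equation with intercept, condition, mediator and two pretests leaves 57 − 5 = 52, which falls to 50 with both race terms. There is some loss of power for 1D even with centred coding (for example 82-94% to 73-82% in the simulated scenarios). No new data are needed.
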